### Patient population

This study requires 200 patients that meet all inclusion criteria.

#### Inclusion criteria

• Left ventricular systolic dysfunction, left ventricular ejection fraction ≤35%, as documented at the moment of ICD implantation;

• Implantation with a wireless-transmission-enabled Medtronic ICD or CRT-D;

• Ability and willingness to undergo remote follow-up instead of scheduled routine in-office follow-up visits;

• Ability to attend all required follow-up examinations at the study center.

#### Exclusion criteria

• Age less than 18 years;

• Unwillingness or inability to give informed consent;

• Life expectancy less than 12 months;

• Participation in another clinical study that may have an impact on the endpoints of the present study.

### Procedures

Patients previously implanted with the above-mentioned devices will be brought in for a standard in-office examination and assessment of the inclusion criteria. After signing an informed consent form and being randomization to either the remote or standard arm, patients will be followed up for a 16-month period, with required visits after 4, 8, 12 months (only for standard arm) and 16 months. In the remote arm CareLink transmissions will replace the 4- and 12-month visits (Figure 1).

Table 1 summarizes the data to be collected at the baseline and during follow-up.

**Table 1 T1:** Overview of data collection requirements

	**Baseline**	**4 Month**	**8 Month**	**12 Month**	**16 Month**
*Demographic/Medical History*	X				

*Device Information*	X				

*Randomization*	X				

*Medications*	X				X

*Healthcare Utilization*	X	X *	X	X *	X

*Alerts*	X	X	X	X	X

*Symptoms*	X	X *	X	X *	X

*Echocardiographic parameters*	X				X

*NYHA Class*	X	X *	X	X *	X

*Save-to-Disk ICD Data*	X	X *	X	X *	X

***Patient Questionnaires***					

*State Trait Anxiety Inventory*	X		X		X

*MLHF*	X				X

*EQ-5D*	X				X

*Patient and Caregiver Burden*	X				

* in Standard Arm only

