**Methods:**

The EVOLVO study is a prospective, randomized, parallel, unblinded, multicenter clinical trial designed to compare remote ICD management with the current standard of care, in order to assess its ability to treat and triage patients more effectively.

Two-hundred patients implanted with wireless-transmission-enabled ICD will be enrolled and randomized to receive either the Medtronic CareLink^® ^monitor for remote transmission or the conventional method of in-person evaluations. The purpose of this manuscript is to describe the design of the trial. The results, which are to be presented separately, will characterize healthcare utilizations as a result of ICD follow-up by means of remote monitoring instead of conventional in-person evaluations.

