### Objectives

The primary objective of the study is to determine whether patients using the CareLink system display a different rate of unplanned cardiac or device-related in-hospital visits from patients in the standard arm. The endpoints for this objective include all cardiac and device-related clinic visits, i.e. all hospital admissions not involving an overnight stay, when the interval between the decision to admit and the admission is <24 hours. The events anticipated to prompt these visits are: ICD alerts regarding system integrity, atrial and ventricular arrhythmias, decrease in intra-thoracic impedance signifying possible fluid accumulation, and patients' symptoms. These endpoints will be subdivided according to whether the visits are related or not related to episodes of worsening of HF; estimation of their respective rates will constitute a secondary objective of the study.

Additionally, the rate and related costs of total healthcare utilizations (all planned and unplanned hospital admissions involving and not involving an overnight stay) for cardiac or device-related events will be compared between groups. For this objective, hospital visits will be also scrutinized and classified as necessary or unnecessary for the clinical management of the patient. In particular, each visit will be judged necessary if it results from an appropriate and clinically meaningful ICD alert (e.g.: intra-thoracic impedance alert associated with clinically deteriorated HF) and if the clinician was not previously aware of the clinical/ICD condition.

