### Design

This is a one-to-one randomized, prospective study. The study has been approved by the Institutional Review Board of the 6 participating Italian centers.

Patients implanted with wireless-transmission-enabled Medtronic ICD or CRT-D will be randomized to "remote transmission on" (remote arm) or "remote transmission off" (standard arm) (Figure 1).

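### Healthcare utilisation is collected every 4 months in the standard arm but every 8 months in the remote arm, which risks under-counting remote-arm visits

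*Protocol article*

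**What the plan says.** Under Procedures, "patients will be followed up for a 16-month period". The standard arm attends at 4, 8, 12 and 16 months. "In the remote arm CareLink transmissions will replace the 4- and 12-month visits", so remote patients attend at 8 and 16 months only.

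In Table 1, the row "Healthcare Utilization" has an asterisk at 4 and 12 months and none at baseline, 8 or 16 months. The footnote defines the asterisk as "in Standard Arm only". The Alerts row has no asterisk at any time point.

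The primary objective asks whether patients using the system "display a different rate of unplanned cardiac or device-related in-hospital visits from patients in the standard arm". A further objective compares "the rate and related costs of total healthcare utilizations". Healthcare Utilization is the only row of Table 1 that records visits, so I take it as the source for both objectives. The abstract describes the study as a "prospective, randomized, parallel, unblinded, multicenter clinical trial".

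**The concern.** The two arms are asked about the outcome at different intensities, and the difference is tied to the randomised allocation. Two mechanisms could lose remote-arm visits:

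- **Longer look-back.** Each post-baseline collection in the remote arm must cover 8 months instead of 4, so more visits may be forgotten or left untraced.
- **Dropout.** A patient who leaves has, on average, a longer uncollected stretch behind them in the remote arm. One who leaves before month 8 has no scheduled post-baseline utilisation record.

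A transmission does not fill the gap. The section on the system describes it as carrying device data such as diagnostics, arrhythmias, therapies and battery or lead status, and hospital visits are not among them.

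The Hypothesis section expects remote patients to need less attention, so any loss would look like benefit. With a planned reduction of only 10%, a modest differential loss matters. Neither the intention-to-treat analysis nor a larger sample would remove it.

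**Working it through.** **Inputs.** From Sample size justification: 2.2 events per person-year, rate ratio 0.90, 20% uniform dropout, 100 patients per group. From Procedures: 16 months of follow-up. From Statistical methods: a two-sided large-sample comparison of incidence rates at 0.05. Allocation is one to one (Design).

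**The plan's own figures.** The base rate reproduces: 140 + 34 + 6 + 40 = 220 episodes, and 220/98 = 2.24 per person-year. The stated power of 99.8% does not. Person-years per arm are 100 × 16/12 × (1 − 0.20/2) = 120, so expected events are 2.2 × 120 = 264 and 0.90 × 264 = 237.6. Then z = 26.4/√501.6 = 1.18 and the two-sided power is 21.8%. That is a separate matter, and this point does not depend on it.

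**Collection schedule.** After baseline the standard arm has 4 collections at 4-month intervals, and the remote arm has 2 at 8-month intervals. If each collection covers the time since the one before, both schedules cover all 16 months for a patient who completes.

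**Dropout mechanism.** This assumes that person-time runs to dropout and that nothing is collected at withdrawal.

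- Dropouts per arm: 0.20 × 100 = 20.
- Leaving before the first post-baseline collection: 20 × 4/16 = 5 (standard) and 20 × 8/16 = 10 (remote).
- Mean time since last collection, half the interval: 2 months (standard) and 4 months (remote).
- Unreported time: 20 × 2/12 = 3.33 and 20 × 4/12 = 6.67 person-years, each out of 120.
- Rate ratio with no true effect: (1 − 6.67/120)/(1 − 3.33/120) = 0.944/0.972 = 0.971.
- Recorded events: 264 × 0.972 = 256.7 and 264 × 0.944 = 249.3. z = 7.3/√506 = 0.33, and the chance of a significant result is about 6.2% against a nominal 5%.

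**Recall loss.** The document gives no figure for this, so the fraction m of remote-arm events unrecorded is an assumption. With no true effect, the remote arm records 264 × (1 − m) events and z = 264m/√(264(2 − m)).

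| m (assumed, acting alone) | Apparent rate ratio | Chance of a significant result |
|---|---|---|
| 0 | 1.00 | 5% (simulated 4.9%) |
| 2% | 0.98 | 5.6% |
| 5% | 0.95 | 9.0% |
| 10% | 0.90 | 21.8% |

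Each row stands alone. Combined with the dropout mechanism, the 5% and 10% rows would become 0.971 × 0.95 = 0.92 and 0.971 × 0.90 = 0.87.

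The probabilities use the plan's 2.2 per person-year as the visit rate. The apparent rate ratios do not depend on that rate.

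**The case against.** The best defence is that unequal frequency is not unequal coverage. The 8- and 16-month cells apply to both arms and can reach back to the previous collection, and nothing says that months 0–4 or 8–12 go unrecorded in the remote arm. The asterisk seems to follow the in-office visit: Save-to-Disk ICD Data carries it too, although a transmission supplies equivalent device data at those months. This stands, and it rules out stating under-counting as a fact.

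Second, patient recall may not be the source. The endpoint is defined by the interval from decision to admission, and visits are judged on whether the clinician already knew of the condition. Both suggest use of records, and a condensed article may leave the data source to the full protocol. This lowers the likely size of any loss. It does not remove the point, because the arm-specific collection rule is stated here, and if continuous capture exists the asterisk misdescribes it.

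Third, the 5% and 10% losses are assumptions, and the 0.97 depends on a person-time rule that an analysis plan would normally set. That is correct, and both are labelled so above.

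Fourth, extra telephone calls would add contact to the arm in which transmissions replace visits, and could prompt symptom reports. This is a fair constraint on the remedy. Collection from records, or contact limited to utilisation questions, meets it.

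**Conclusion.** The point holds as a risk of differential ascertainment of the primary endpoint, in the hypothesised direction, in an unblinded trial. Total utilisation and costs share it. The only size that uses the plan's own inputs is a rate ratio of about 0.97 under no effect, with type I error of about 6%, and it needs both assumptions on person-time and withdrawal. An assumed 10% recall loss would by itself match the whole planned effect, but the document gives no reason to choose that figure.

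A reader might infer three stronger things that the document does not support:

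- **Remote-arm visits are in fact under-counted.** The later collections may cover the whole period for completers.
- **Half of remote follow-up is lost, giving a rate ratio of 0.50.** The document nowhere says that those months are unrecorded.
- **Clinical status is biased in the same way.** NYHA class and symptoms are collected in both arms at baseline, 8 and 16 months, and the document does not say that the 4- or 12-month values enter any endpoint.

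The change is worth making because it is cheap and protects the primary comparison. I would not call it mandatory, and my confidence is moderate.

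**What to change.** 1. Remove the asterisk from Healthcare Utilization in Table 1. Ascertain visits in both arms at 4, 8, 12 and 16 months, on the same form and with the same stated look-back. Hospital or centre records are the preferred source. Failing that, make a brief contact in the remote arm at the 4- and 12-month transmissions, restricted to utilisation questions.
2. Collect utilisation at withdrawal in both arms.
3. End each patient's person-time at the last date on which utilisation was ascertained. This alone removes the dropout mechanism, because events and person-time then stop together, but it does not address recall.
4. For patients already past month 4 or 12, complete those windows from centre records in both arms.

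The cost is a form change, one line on person-time, and either record review or at most two short contacts per remote patient. The drawback is a small site workload and, if contact is used, the need to keep it from altering the remote intervention.

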### Device programming

Initial ICD programming is to be performed at the time of randomization. Tables 2 and 3 show detailed lists of all protocol-required device programming parameters.

**Table 2 T2:** Alert programming. Clinical Management Alerts

	**Remote Arm**	**Standard Arm**
***Intra-thoracic Impedance Monitoring (OptiVol Alert)***		

*OptiVol Alert – Device*	Off	On

*OptiVol Alert – Monitor*	On	Off

***AT/AF Burden and Rate Settings***		

*AT/AF Daily Burden Alert Enable – Device **	Off	On

*AT/AF Daily Burden Alert Enable – Monitor **	On	Off

*- Daily AT/AF Alert Burden*	6 hours	6 hours

*Avg. V. Rate During AT/AF Alert Enable – Device ***	Off	On

*Avg. V. Rate During AT/AF Alert Enable – Monitor ***	On	Off

*- Avg. V. Rate During AT/AF*	100 beats/min	100 beats/min

*- Daily Burden for Avg. V. Rate*	6 hours	6 hours

***Number of Shocks Delivered during an Episode***		

*Alert Enable – Device*	Off	Off

*Alert Enable – Monitor*	On	Off

*- Threshold Number of Shocks*	1	-

***All Therapies in a Zone Exhausted for an Episode***		

*Alert Enable – Device*	Off	On

*Alert Enable – Monitor*	On	Off

* To pursue a "Rhythm Control" strategy; ** To pursue a "Rate Control" strategy

**Table 3 T3:** Alert programming. Lead/Device Integrity Alerts

	**Remote Arm**	**Standard Arm**
*Patient Home Monitor*	On	Off

***Lead Impedance Out of Range*** **(*A. pacing, LV pacing*, RV pacing, RV defibrillation, SVC defibrillation***)**		

*Alert Enable – Device*	On-High	On-High

*Alert Enable – Monitor*	On	Off

***Low Battery Voltage RRT***		

*Alert Enable – Device*	On-High	On-High

*Alert Enable – Monitor*	On	Off

***Excessive Charge Time EOS***		

*Alert Enable – Device*	On-High	On-High

*Alert Enable – Monitor*	On	Off

***VF Detection/Therapy Off***		

*Alert Enable – Device*	On-High	On-High

*Alert Enable – Monitor*	On	Off

* For systems with an LV lead; ** For systems with dual-coil leads

In summary, all alerts regarding clinical management (intra-thoracic impedance for fluid accumulation monitoring, atrial arrhythmias, ICD shocks delivered) will be turned on for wireless notification through the CareLink in the remote arm, while no audible alerts will be used. In the standard arm these alerts will be turned on for audible notification only.

All lead and device integrity alerts will be turned on for both wireless and audible notification in the remote arm, and for only audible notification in the standard arm.

In the standard arm, audible alerts for intra-thoracic impedance monitoring will be programmed to sound at a different time of the day from alerts for other causes, in order to distinguish them.

Clinicians are allowed to turn off the alert for atrial arrhythmias, if they are no longer attempting to control the subject's atrial rhythm. Similarly, they can turn off the alert for intra-thoracic impedance when recurrent inappropriate detections of fluid accumulation are documented.

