### Rationale for design

Currently, outpatient follow-up examinations of ICD patients are scheduled at regular 3- to 6-month intervals [8,9]. In the present study, we will compare a standard arm undergoing 4 in-office examinations per year with a remote arm in which 2 of the 4 examinations are replaced by remote interrogations, as previously proposed [16,17].

Acute events, such as ICD shocks, alerts or symptoms that usually prompt the subject to seek urgent attention at the clinic, will be managed via CareLink and telephone follow-up in the remote arm. Indeed, it has been recently shown that a considerable portion of post-shock interrogations do not involve reprogramming of the ICD and may therefore be performed remotely [10,15].

The audible alert feature has been shown to facilitate the early discovery of serious ICD complications [7], and improved alert algorithms have recently been implemented to detect lead failures promptly [6]. Similarly, in view of the high incidence of atrial fibrillation in HF [18] and the consequent increased risk of decompensation, stroke and inappropriate shocks, the advanced ICD capabilities for detecting atrial arrhythmias have the potential to play a growing role in patient monitoring [5]. By providing remote notification and access to details of the occurrence and duration of atrial fibrillation and ventricular response, CareLink will facilitate the management of therapies for rhythm or rate control and the prompt administration of anticoagulants for stroke prevention.

Continuous intra-thoracic impedance monitoring in modern ICD is intended to detect HF decompensation promptly, thereby permitting early therapeutic intervention [4]. Decreased intra-thoracic impedance has been shown to reliably identify acute HF, with low rates of undetected events [19], and to be associated with an increased risk of HF hospitalization [20]. As recently shown [15], a high percentage of episodes may be successfully and promptly managed through CareLink without requiring additional in-hospital visits, by means of remote data review and assessment of symptom status and therapy compliance by phone. Moreover, patients might not hear or respond to the audible impedance alert, as recently reported [21]. Thus, automated telemetric transmission of alerts to the physician may shorten the delay between alert and therapy initiation, further improving the clinical outcome.

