Other trials have used a control arm blinded to device data [22], in order to test the clinical value of diagnostic features. By contrast, in the present study all alerts will be turned on for audible notification in the standard arm and the diagnostics will be open for in-office review. This will enable the benefits associated to remote notification and access to ICD data to be specifically assessed in addition to the diagnostic and alerting capabilities of modern ICD.

Another trial is currently investigating the CareLink system in pacemaker patients [23]. The present study on ICD/CRT-D patients, however, will focus on a sicker population with more complex devices. This is the setting in which remote monitoring is presumed to offer the greatest benefits.

In the hypothesis of a more stable clinical status of the patient and a reduced need to adjust ICD parameters 6 months after implantation [10], stratifying patient randomization on the basis of time since implantation will limit a potential bias.

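### The standard-arm shock alert is Off in Table 2 but audible in the text, so the comparator is stated in two ways

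*Protocol article*

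**What the plan says.** **Shock alert.** The summary after Table 3, in the Device programming section, defines the clinical alerts as "all alerts regarding clinical management (intra-thoracic impedance for fluid accumulation monitoring, atrial arrhythmias, ICD shocks delivered" and closes the list there. It says that they are wireless in the remote arm, and of the comparator: "In the standard arm these alerts will be turned on for audible notification only". The Discussion (Rationale for design) says that "all alerts will be turned on for audible notification in the standard arm", and gives this as the reason why the trial can isolate the benefit of remote notification and access. The Design section likewise says that standard-arm devices keep all their features, audible alerts included, without the network.

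Table 2 has a separate block titled "Number of Shocks Delivered during an Episode". In the standard arm both its Device and Monitor settings are Off and the threshold cell holds a dash. In the remote arm the Device setting is Off, Monitor is On and the threshold is 1. The opening of the Device programming section describes Tables 2 and 3 as the programming that the protocol requires.

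**Visit frequency.** The Discussion describes "a standard arm undergoing 4 in-office examinations per year", of which two are replaced by remote interrogation in the other arm. The Procedures section says "patients will be followed up for a 16-month period, with required visits after 4, 8, 12 months" and adds a visit at 16 months; transmissions replace months 4 and 12 in the remote arm. Table 1 has the same time points.

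**The concern.** The trial compares two ways of delivering alert information, so the alert settings in the standard arm are part of the definition of the comparator. If the text holds, a shock generates an audible alert in one arm and a wireless alert in the other, and the arms differ in the route. If Table 2 holds, the number-of-shocks alert exists in the remote arm only, and the arms also differ in whether that alert is issued at all. The Discussion's attribution to remote notification and access depends on the first situation.

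This bears on the primary objective because the Background and the Discussion both name shocks among the events that bring patients in for unscheduled care. There is also an operational problem: sites programming from the table and sites programming from the text would deliver different comparators.

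The visit-frequency mismatch is of a lower order. It describes the comparator inexactly, in a rationale paragraph.

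**Working it through.** **Step 1. Alert settings side by side** (Table 2; Device is audible, Monitor is wireless).

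| Clinical alert | Remote: Device / Monitor | Standard: Device / Monitor | Agrees with the text for the standard arm? |
|---|---|---|---|
| Intra-thoracic impedance | Off / On | On / Off | Yes |
| AT/AF daily burden | Off / On | On / Off | Yes |
| Ventricular rate during AT/AF | Off / On | On / Off | Yes |
| Number of shocks | Off / On (threshold 1) | Off / Off (threshold: dash) | No |
| All therapies in a zone exhausted | Off / On | On / Off | Yes |

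In Table 3 the four integrity alerts (lead impedance, battery, charge time, VF detection or therapy off) are audible in both arms and wireless in the remote arm only, as the text says. So 8 of the 9 alert groups agree with the Discussion's statement and one does not. The shock row is complete, and its dash is what one would expect for an alert that is Off, so a cell lost in reading the table is unlikely.

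**Step 2. Weight of shocks in the planning data** (Sample size justification).
- The plan's own figure: 140 + 34 + 6 + 40 = 220 episodes, and 220 / 98 person-years = 2.24, stated as 2.2. It is reproduced.
- Share of shocks: 40 / 220 = 18.2%.
- Shock rate: 40 / 98 = 0.41 per person-year.

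These are device episodes in a planning population, not visits.

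**Step 3. Visit frequency** (Procedures and Table 1).
- Follow-up is 16 / 12 = 1.333 years.
- Standard arm: 4 visits / 1.333 = 3.0 per year, against 4 per year in the Discussion. The stated figure is not reproduced.
- Remote arm, in-office visits at months 8 and 16: 2 / 1.333 = 1.5 per year.
- Counting baseline as an examination: 5 / 1.333 = 3.75 per year over the 16 months.
- Four per year would require 4 × 16 / 12 = 5.3 visits in 16 months.

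**The case against.** **The shock mismatch may matter little in practice.** The Discussion says that shocks usually lead patients to seek urgent care. Figure 2 is captioned as covering device shocks as well as alerts in the standard arm, so a shock there has a management pathway without an alert. The therapies-exhausted alert is also audible in that arm. This stands as a limit on the consequence. It does not remove the contradiction, because Table 2 gives the number-of-shocks alert its own block and the text names delivered shocks expressly.

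**A reader might infer that 18% of the primary endpoint is affected.** The documents do not support that. The 18% is a share of planning episodes. The primary endpoint counts unplanned cardiac or device-related visits, which system-integrity alerts and symptoms can also prompt, and nothing says that each episode produces a visit.

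**A reader might infer that the visit-frequency mismatch distorts the utilisation and cost comparison.** This is not supported either. Procedures and Table 1 agree on the schedule, visits will be counted under it, and neither the Statistical methods nor the sample size uses the annual figure. Fewer scheduled visits in the remote arm are the intended intervention, so a utilisation ratio built from the schedule would measure that and not the inconsistency. Counting baseline with months 4, 8 and 12 would give four examinations in the first year, but the article does not say that this is meant.

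**Reporting the primary result without shock-prompted visits** is not called for. It would select visits by a cause that arises after randomisation and whose detection may itself differ by arm.

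**Conclusion.** The contradiction on the shock alert is real and operative. The required programming in Table 2 and the statements in Device programming and the Discussion cannot all hold, and the Discussion's claim about what the comparison isolates depends on which one does. It is confined to one of nine alert groups. Its effect on the primary visit rate cannot be derived from the article and may be smaller than the 18% episode share suggests, since patients may present after a shock without an alert. Sample size, power, endpoint definition and test are unaffected.

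The conclusion assumes only that the Table 2 row was read correctly, which its internal consistency supports. It takes no position on which setting is right.

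The four-per-year phrase is a minor wording error in a rationale paragraph. The figures of four examinations and two replaced match the schedule; the unit of time does not.

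**What to change.** - Reconcile the Design section, the summary in Device programming and the Discussion (Rationale for design) with Table 2, so that a single standard-arm setting for the number-of-shocks alert is stated. The choice belongs to the sponsor and the investigators.
- Document what was actually programmed in each arm. Table 1 lists Save-to-Disk ICD data, but the article does not say whether these files hold alert settings, so the source has to be confirmed.
- If the setting differed by arm, limit the Discussion claim: for shocks the arms then differ in the existence of that alert as well as in remote notification and access.
- As a wording correction, reconcile the annual visit figure in the Discussion with Procedures and Table 1, for example by giving visits per 16 months.

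The cost is a few sentences of text and a check of programming records. No change to sample size or analysis is needed.
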